### Work package 4: community identification, referral and outcome assessment of people with SMDs (months 24–48)

Our aim for WP4 is to determine whether our interventions lead to an increase in numbers of people with SMDs accessing biomedical care. We will further ascertain these individuals’ initial and follow-up mental health status and quality of life, reduction in caregiver burden, and changes in community attitudes and help-seeking for SMDs. We will collect data pre-intervention to identify the number of people with SMDs attending mental health services from the study site and their basic clinical and sociodemographic characteristics. Data collection systems will be in place for baseline and follow-up assessments of successive patients identified with signs of SMD and enrolled into the study over 12 months.

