#### Quantitative evaluation

In WP4, we will adopt a two-fold approach. Primarily, we will assess the impact of the proposed intervention on the (mental health) care pathway of individuals with SMDs and its potential effect on their health status. We will assess impact on the referral pathway by comparing referral rates made to the participating healers 12 months before and after intervention (training) is delivered. We will undertake a pre–post regression analysis to quantify the referral difference at the healer level after adjusting for healers’ and patients’ characteristics. Both the crude and the adjusted rate change and its corresponding 95% confidence interval will be provided.^38^ The change in referral rate will be the primary outcome of interest for this study.

We acknowledge that some participants may be directed to biomedical services by a healer but, for various reasons, may not actually access biomedical care. To further evaluate the impact of a healer's referral, we will try our best to trace their referrals and find out whether potential participants used mental health clinics.

In addition to the primary outcome, a number of patient-related secondary outcomes will be analysed. At this (patient) level, analysis will focus on clinical outcomes, functioning, participant and family satisfaction, medication adherence and attendance for clinical follow-up (Table 1 outlines the measures and time points for assessments).Uptake of healthcare will be evaluated longitudinally: at baseline (i.e. intake) and at months 1, 2 and 3. Similarly, clinical outcomes will be assessed longitudinally using the Global Assessment of Symptoms (GAS), Global Assessment of Functioning (GAF) and clinician-rated primary and secondary diagnoses. Carer burden will be assessed at baseline and post-intervention at month 3 using the Perceived Family Burden Scale (PFBS), and family satisfaction will be assess longitudinally using the Verona Service Satisfaction Scale (adapted to LMIC contexts). We will investigate service utilisation and associated costs using the abbreviated version of the Client Services Receipt Inventory (CSRI) – modified as used in our previous study.^39^ We will employ a linear mixed model to estimate longitudinal changes, adjusting for patient characteristics, time and baseline values/scores. Estimates and effect sizes will be reported, together with their 95% confidence intervals.

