**Table 1 tab01:** Primary and secondary outcomes to be collected and their corresponding time points

		Assessment time point							
Domain	Tool	Pre-intervention	Baseline/intake	Month 1	Month 2	Month 3	Post-intervention	Analysis plan	Estimates reported
Number of individuals from study sites accessing biomedical care	Review of health record systems at NIMH in Dhaka (Bangladesh) and Ibadan (Nigeria)	✓					✓	Pre–post analysis	Referral rate and 95% CI
Number of referrals made by CHWs and traditional and faith healers	For each referral, CHWs will record date of referral and referral source (e.g. self, family member, faith or traditional healer)						✓	Pre–post analysis	Referral rate and 95% CI
Pathways to care (number and type of help-seeking contacts made prior to accessing biomedical care, and duration of untreated illness)	Nottingham Onset Schedule (NOS)		✓				✓	Pre–post analysis	Referral rate and 95% CI
Clinical characteristics of individuals accessing biomedical care	See assessment below	✓					✓	Longitudinal	Mean change since baseline
Sociodemographic profile									
	Age	✓	✓				✓	Longitudinal	Mean change since baseline
	Gender	✓	✓				✓	longitudinal	Mean change since baseline
	Education level		✓					Baseline only	descriptive only
	Religious background	✓	✓				✓	Longitudinal	Mean change since baseline
	Employment status		✓					Baseline only	Descriptive only
	Socioeconomic status		✓					Baseline only	descriptive only
	Family and marital status		✓					Baseline only	Descriptive only
	Area of residence	✓					✓	Longitudinal	Mean change
	Number of children <18 years old	✓	✓					Pre-intervention/baseline only	Descriptive only
Symptom severity	Global Assessment of Symptoms (GAS)		✓	✓	✓	✓		Longitudinal (baseline, months 1, 2 and 3)	Mean change (repeated measures)
Clinical/symptom profile	Clinician-rated primary and secondary diagnoses as recorded in charts		✓					Baseline only	Descriptive only
Level of functioning	Global Assessment of Functioning (GAF)		✓	✓	✓	✓		longitudinal (baseline, months 1, 2 and 3)	Mean change (repeated measures)
Physical health	Body mass index (BMI)		✓			✓		Longitudinal (baseline, month 3)	Mean change (repeated measures)
Carer burden	Perceived Family Burden Scale (PFBS)		✓			✓		Month 3 only	Descriptive only
Engagement with services	Record each month of whether patient contacted treatment provider and type of contact (phone, in-person, etc.).			✓	✓	✓		Longitudinal (months 1, 2 and 3)	Rate change (repeated measures)

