Service utilisation and costs	Abbreviated version of modified version of Client Services Receipt Inventory (CSRI)		✓			✓		Longitudinal (baseline, month 3)	Mean/rate change (repeated measures)
Medication adherence	Medication Adherence Rating Scale (MARS)			✓	✓	✓		Longitudinal (months 1, 2 and 3)	mean change (repeated measures)
Patient and family satisfaction with services	Verona Service Satisfaction Scale (adapted to LMIC contexts)			✓	✓	✓		Longitudinal (months 1, 2 and 3)	Mean change (repeated measures)
Quality of life	EuroQoL five dimensions questionnaire (EQ-5D)		✓			✓		Longitudinal (baseline, month 3)	Mean change (repeated measures)

CHW, community health worker; NIMH, National Institute of Mental Health; LMIC, low- and middle-income country.

We will follow checklists such as the STROBE Statement to report our observational research. We are intending to develop a dedicated statistical analysis plan (SAP) with detailed description of the analyses undertaken (primary and sensitivity), the handling of missing values and model-assumption violations. The alpha = 0.05 significance level will be used in all analyses.

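### Carer burden is collected at baseline and month 3 to look for a reduction, but its Table 1 row analyses month 3 alone, descriptively

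*Protocol article*

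**What the plan says.** Three places in the protocol article bear on carer burden.

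- **Aim.** The Work package 4 section lists among the things to be ascertained a "reduction in caregiver burden, and changes in community attitudes and help-seeking for SMDs".
- **Data collection.** The Quantitative evaluation section says "Carer burden will be assessed at baseline and post-intervention at month 3 using the Perceived Family Burden Scale (PFBS". In the carer burden row of Table 1 the baseline/intake and month 3 columns are ticked, and no others.
- **Analysis.** In the same row, the analysis-plan column restricts the analysis to month 3, and the estimates column reads "descriptive only".

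The Quantitative evaluation section also has a general statement on the secondary outcomes: "We will employ a linear mixed model to estimate longitudinal changes, adjusting for patient characteristics, time and baseline values/scores". It promises estimates and effect sizes with 95% confidence intervals, and it does not name the PFBS.

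**The concern.** A reduction is a difference between two time points. A month 3 summary gives the level of burden at that visit and nothing about where carers started. If the Table 1 entry is followed, the baseline scores are collected and then left out of the analysis, and the aim named in Work package 4 gets neither an estimate nor an interval.

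The data needed to answer the question will be in hand, so what is at stake is whether the published plan uses them. If the row stands, an analyst who follows it cannot address the aim. An analyst who reports a change departs from a published plan, and that change then looks unplanned.

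**Working it through.** There is no figure to reproduce: the article gives no sample size, standard deviation, score range or target difference for the PFBS. The check is a comparison of entries.

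**Step 1: aim, data and analysis for the PFBS.** The aim requires a comparison of two visits. The text and the ticks agree that both visits are measured. The analysis cell keeps one of them. The first two entries fit together and the third does not. The two analysis cells also fail separately. A descriptive summary of both visits would at least have shown the direction of change. A month 3 summary cannot, whatever the number of carers.

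**Step 2: other rows with the same visits.** Four outcomes in Table 1 are ticked at baseline and month 3 and nowhere else.

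| Outcome | Analysis in Table 1 | Estimate in Table 1 |
|---|---|---|
| BMI | longitudinal, both visits | mean change |
| Service use and costs (CSRI) | longitudinal, both visits | mean or rate change |
| Quality of life (EQ-5D) | longitudinal, both visits | mean change |
| Carer burden (PFBS) | month 3 alone | descriptive |

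The first three carry the entry "Longitudinal (baseline, month 3" (closing bracket omitted). The PFBS is the exception among the four, and no reason is given.

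**Step 3: other rows marked as descriptive.** There are six: education, employment, socioeconomic status, family and marital status, number of children, and clinician-rated diagnoses. In Table 1 each is ticked only at baseline, or at pre-intervention and baseline. Carer burden is the only outcome with a follow-up visit that is treated this way, although it is one for which Work package 4 names a direction of change.

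**Step 4: does the general model sentence settle it?** There are two readings.

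- If the sentence covers the PFBS, the text promises a change with a 95% confidence interval while the table promises a month 3 description. The article then contradicts itself.
- If it does not, the Table 1 row is the only analysis plan for the PFBS, and it cannot meet the aim.

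The surrounding text does not decide between them. The section describes uptake, clinical outcomes and family satisfaction as longitudinal but does not use that word for carer burden. Its statement of focus also omits it: "analysis will focus on clinical outcomes, functioning, participant and family satisfaction, medication adherence and attendance for clinical follow-up". Against that, the model sentence is not limited to named scales, and BMI and EQ-5D are not named in it either. On both readings the Table 1 row needs correcting.

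**The case against.** The strongest reply is that the mixed-model sentence comes two sentences after the PFBS sentence, in the same paragraph on secondary outcomes, and would naturally be taken to cover a scale measured twice. On that view the table cell is a drafting slip. Table 1 is loose elsewhere: gender and religious background are assigned a mean change, and diagnoses are baseline-only in the table but longitudinal in the text. The section cites Table 1 for measures and time points, not for methods, and a dedicated SAP is announced.

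Much of this stands. A reader might infer from the row that a reduction in carer burden will never be estimated. The article does not support that, because the general model may be meant to include the PFBS and the SAP is not shown. A slip is also at least as likely as a deliberate choice.

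What does not stand is that nothing needs changing. The SAP may supply detail that an article omits, but here the article states an analysis, and the one stated does not fit its own aim. A slip in the only PFBS-specific entry still has to be put right.

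It is also fair to say that this is one secondary outcome, that no data are lost, and that a corrected row would still give only a before-and-after change without a control group.

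**Conclusion.** The point holds as an internal inconsistency. The only analysis entry specific to the PFBS leaves out the baseline and cannot show the reduction that Work package 4 sets out to ascertain. It departs from the handling of the three other outcomes with the same two visits and, if the general mixed model is meant to cover the PFBS, it contradicts that too.

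Its extent is two cells in one row, for one secondary outcome. The primary outcome, the change in referral rate, is not affected. No loss of precision or power can be quantified from the article, and the conclusion does not depend on any such figure. It rests only on reading the aim as a change between visits and the Table 1 cells as meaning what they say.

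**What to change.** In the carer burden row of Table 1:

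- replace the analysis entry with the one used for BMI, CSRI and EQ-5D, "Longitudinal (baseline, month 3" (plus its closing bracket);
- replace the estimate entry with mean change and 95% CI, from repeated measures.

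State in the text that the result is an uncontrolled within-carer change, so that it is not read as an effect of the intervention. Say also whether the general mixed model covers the PFBS. The exact change model, including how the baseline score enters, can be left to the SAP.

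If a month 3 description really is what the investigators intend, the alternative is to remove the reduction in caregiver burden from the Work package 4 aim.

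The cost is two table cells and one or two sentences, with no extra visit, instrument or participant. The change should be made before carer outcome data are analysed, so that the estimate is prespecified.

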### Management

The University of Warwick is the sponsor organisation. A programme manager is responsible for the day-to-day management of the project and supports the principal investigator on the project's overall delivery. The programme manager, principal investigator and work package leads are responsible for the overall management of the study and meet monthly by video conference chaired by the principal investigator. The project steering committee (PSC), comprising the programme manager, principal investigator, co-investigators and work package leads, provides overall strategic direction, ensures good governance, provides scientific input, guides capacity-building activities and provides financial probity when required.

An independent external scientific advisory board (ESAB) of international experts will monitor and assess the study conduct and progress. Both the PSC and ESAB will meet annually with the consortium to assess the scientific quality of the research and provide feedback.

### Ethics

Informed consent will be obtained from all participants as appropriate, before their enrolment into the study. We will develop a clinical care pathway for participants that will ensure safety, protection of confidentiality and privacy. The research team will preserve the confidentiality and anonymity of participants taking part in the study and fulfil transparency requirements under the UK General Data Protection Regulation for health and care research, with equivalent guidance from Nigeria and Bangladesh. The study may be subject to inspection and audit by the University of Warwick under their remit as sponsor and by other regulatory bodies to make sure of adherence to good clinical practice (GCP) and the UK Policy Framework for Health and Social Care Research.

The TRANSFORM team will apply for ethics approval specific to each work package from the University of Warwick's Biomedical and Scientific Research Ethics Committee, Coventry, UK, and the research ethics committees of all participating organisations. The ethical conduct of the study is monitored throughout by the University of Warwick and each participating organisation.

### Dissemination

We will engage with our strong network of stakeholders involved in mental health services, such as clinicians, academics, service providers, policy makers, governmental and non-governmental agencies, community groups, patient and carer advocacy groups, media agencies and the creative arts industry, to support dissemination activities and public engagement across a variety of academic and non-academic audiences. We will (a) develop and maintain an up-to-date project website and social media page(s) (to target different audiences/stakeholders); (b) present study findings at national and international psychiatric and mental health scientific conferences and in peer-reviewed publications; and (c) disseminate our findings as broadly as possible in Bengali and Yoruba through film, radio and street theatre developed with local creative partners and civil society advocacy groups. We will work closely with our partners to identify the dissemination and public engagement approaches that will work best in these settings, to increase the impact of our research, to further engage the target communities, raise awareness, reduce stigma and provide information on plural healthcare for SMD.

### Patient and public involvement

We have strong and ongoing engagement with various internal and external stakeholders involved in mental healthcare. Patient and public involvement (PPI) is at the heart of TRANSFORM, and the entire study was conceived with people with lived experience of SMDs, their families, faith healers, charity organisations and the wider community. WP1 uses participatory approaches to understand local and contextual understandings of mental health, illness and help-seeking behaviour from the perspective of patients and carer groups and voluntary/charity/third-sector organisations, ensuring representation of hard-to-reach groups. The community were involved in proposing the research objectives and in the overall study design and will be central to the implementation of our intervention; and co-author [name] is an expert on Yoruba history and *Ifa* divination, a traditional healer and co-investigator. All researchers and partners in TRANSFORM also have an extensive record of patient and carer involvement in research. We have a robust programme for monitoring and governance – research, ethics and financial – and our programme will adhere to the highest levels of ethical practice and probity, including PPI.

## Discussion

The TRANSFORM study plans to build on lessons learned from previous research in this area, particularly from the University of Ibadan, which is a centre of excellence and WHO Collaborating Centre for mental health research. The University of Ibadan has been the site of a significant number of influential studies on SMI and help-seeking which have led to several high-quality publications, including, but not limited to:
INTREPID 1 and 2 – social epidemiological and qualitative research on methods of community case finding and help-seeking pathways for psychosis (funded by the Medical Research Council) (e.g.^40^)PAM-D – formative qualitative research on local concepts of mental health and explanatory models (funded by the US National Institute of Health) (e.g.^27^)COSIMPO – a cluster randomised controlled trial of a collaborative care model for psychosis with traditional and faith-based healers and primary care mental health workers (funded by the US National Institute of Mental Health).^25^

TRANSFORM will build on these studies, elaborating and extending understanding through its distinctive methodology and approach, including:
evaluating impact and effectiveness as the primary outcometargeting people with all SMDs, including severe depression, not just psychosisdeveloping a help-seeking pathway and provision from the community, through various care pathways (primary and secondary care) with follow-updeveloping a clear referral pathway to existing mental health servicestraining primary care workers/CHWs to screen for SMDs and refer, rather than using specialist mental health nurses, in line with the integration of mental healthcare into primary careincreasing collaboration, understanding and respect between mental health workers, including psychiatrists, nurses and CHWs, and healers of different types through a strong focus on participatory methods and community engagementcomparison between Nigeria and Bangladesh rather than another country within Africa.

TRANSFORM also aims to innovate methodologically through:
using mixed methods, in particular ethnography and participatory methods, in addition to qualitative interviews and quantitative methodsinvolving the community, including people with lived experience, caregivers and other stakeholders, from the outset and throughout the process through community advisory groups and other participatory methods, with a view to building in sustainabilityusing results of initial ethnographic research on existing help-seeking practices as well as the activities of healers and primary health workers to inform training (WP2), intervention (WP3) and evaluation (WP4 and WP5).co-producing training with CHWs, mental health workers and healersconducting both process and outcome evaluation using mixed methods, including ethnography and qualitative interviews to understand how, why and for whom the intervention was or was not successful.

## Conclusions

The sizeable differences in social and cultural context, lived experience, sociodemographics, infrastructure and availability of resources mean that models of care developed in high-income countries cannot be simply translocated to LMICs.^39^ TRANSFORM will co-develop a novel and sustainable referral pathway for people with SMDs to access biomedical care, while engaging with the benefits of existing pluralistic help-seeking pathways. We will tailor evidence-informed interventions to the local sociocultural context to address the increasing burden of SMDs in Nigeria and Bangladesh. By developing a novel intervention that is regionally relevant, TRANSFORM will develop and test sustainable interventions that can be integrated into existing clinical care and generate data (including health economic data) that will inform priorities for healthcare providers and policy makers.

## Data Availability

Data availability is not applicable to this article as no new data were created or analysed in this report.
